## Abstract

**Background:**

In patients with prostate cancer (PCa) with histopathologically proven pelvic lymph node (LN) metastasis (pN1) after extended pelvic lymph node dissection (ePLND), multimodality treatment consisting of treatment of the primary tumor and whole pelvic radiotherapy (WPRT) combined with androgen deprivation therapy (ADT) offers promising results, leading to better cause-specific survival rates compared with ADT alone. However, in case more than one pelvic LN is invaded by the tumor, approximately 40% of the patients relapse biochemically and clinically. Clinical relapse is present in the para-aortic LNs (M1a disease) in up to 77% of the relapsing cases.

**Objective:**

We hypothesize that, based on the evidence that positive LNs represent the door to hematogenous dissemination, elective para-aortic irradiation will reduce the development of both retroperitoneal nodal (M1a) and distant metastasis (M1b or M1c disease), postpone the need for palliative ADT, and prolong the time to castration-refractory disease.

**Methods:**

To test this hypothesis, we will conduct a prospective, nonrandomized phase II trial to study the efficacy of additional elective para-aortic radiotherapy (PART) in pN1 patients compared with those who were historically treated with adjuvant WPRT alone. We aim to include 137 patients with PCa and presence of pN1 disease after ePLND. With this number of patients, an improvement of 15% in the 5-year clinical relapse-free survival can be detected with a power of 80%.

**Results:**

Recruitment of patients for this trial started in 2017 and will be completed approximately by March 2020.

**Conclusions:**

This is the first phase II trial to investigate the benefits of an elective PART in patients with PCa. The results of this trial will potentially serve as a sound base for a later randomized phase III trial. All participants are given a PART information sheet and required to give written informed consent. Results are expected to be published in a peer-reviewed journal.

**Trial Registration:**

ClinicalTrials.gov NCT03079323; https://clinicaltrials.gov/ct2/show/NCT03079323 (Archived by WebCite at http://www.webcitation.org/73ELimv1d)

**International Registered Report Identifier (IRRID):**

PRR1-10.2196/11256

## Introduction

Prostate cancer (PCa) is the most common nonskin malignancy and an important cause of cancer-related mortality in men in industrialized countries worldwide [1,2]. Mortality is highest in patients with high-risk PCa, defined by the guidelines of the European Association of Urology (EAU) as T-stage ≥cT2c or Gleason score ≥8 or prostate-specific antigen (PSA) >20 ng/mL. These patients benefit from aggressive local treatment (surgery with or without adjuvant radiotherapy or primary radiotherapy). To assess the risk of disease spread to pelvic nodes, predictive nomograms are used [3-5], although the EAU guidelines consider an extended pelvic lymph node dissection (ePLND) as a necessity in high-risk patients [6]. Indeed, ePLND has proven to be the most accurate nodal staging procedure and, therefore, remains the gold standard [7] with even a positive effect on PCa mortality, certainly in case of limited nodal disease [8] and negative nodes [9].

Historically, patients with positive pelvic lymph nodes (LNs; N1) were considered metastatic and treated with lifelong palliative androgen deprivation therapy (ADT) only [10]. However, in the 21st century, an important paradigm shift occurred. First, local treatment with curative intent is gaining interest in patients with N1 disease [11]. Hereby, also the extent of ePLND plays a crucial role in predicting cause-specific survival (CSS) as demonstrated by Abdollah et al [12]. Second, large retrospective series demonstrated an improvement in prostate cancer-specific survival (PCSS) when postoperative radiotherapy was added to ADT in pathologically node-positive (pN1) patients [13-15].

In the multidisciplinary approach for pN1 patients, multimodality treatment consisting of treatment of the primary tumor, long-term ADT, and whole pelvic radiotherapy (WPRT) has become the standard of care at the Leuven University Hospitals (LUH; Leuven, Belgium) and at the Ghent University Hospital (GUH; Ghent, Belgium). WPRT is delivered using intensity-modulated or volumetric modulated arc therapy (IMAT/VMAT) [16,17]. Clinical results demonstrated that this multimodality treatment is well tolerated and results in 5-year PCSS of >90%, with the best results observed in patients having a low number of positive LNs. Indeed, patients presenting with 1 or 2 positive LNs had a 5-year PCSS comparable to that of pN0 patients [18-20].

The number of pathologically metastatic LNs is a determinant for patient outcome. In case >2 LNs are pathologically invaded by the tumor, 30%-40% of the patients relapse biochemically and clinically [21,22]. Furthermore, some data suggest that extracapsular extension of pelvic nodal metastases is an important negative prognostic factor in pN1 patients [23].

Reportedly, clinical relapse (cR) is present in the para-aortic LNs (PALN, M1a disease) in up to 77% of the cases [24,25]. Rischke et al demonstrated the retroperitoneum to be the most frequent site of relapse after pelvic salvage treatment [26]. In the TNM classification, patients with positive PALN are denominated M1a disease and considered as a separate entity [27]. We hypothesize that these positive PALNs will lead to further hematogenous spread (M1b-M1c disease [27]) and that elective para-aortic irradiation will decrease the rate of further metastatic spread, postpone the need for palliative ADT, and prolong the time to castration-refractory disease. To test this hypothesis, we designed a prospective, nonrandomized phase II trial to evaluate the efficacy of elective para-aortic radiotherapy (PART) in pN1 patients compared with those who were historically treated with adjuvant WPRT alone (Figure 1).

This trial is novel and unique as it is the first to investigate the irradiation of the PALN region in pN1 patients with PCa to prevent further metastasis. This strategy has already been evaluated in advanced cervical cancer, but to the best of our knowledge, never in patients with PCa.

**Figure 1 figure1:**
[figure not shown]
Graphic presentation of the study hypothesis.

## Methods

### Study Design

The PART trial is a nonrandomized phase II trial that was approved by the Medical Ethical Committee of the LUH (EC number: B 3222 0163 0604) and is written in accordance with the Standard Protocol Items: Recommendations for Interventional Trials guidelines. Patients are recruited during the multidisciplinary consultation Urology-Radiation Oncology and at the Department of Radiation Oncology of the LUH, GUH, and other participating centers. After giving informed consent, they are included in the trial.

### Inclusion and Exclusion Criteria

Men aged >18 years with histologically proven adenocarcinoma of the prostate at biopsy (cT1-4) who are referred for primary high-dose radiotherapy or patients after radical prostatectomy (RP; pT2-4) with presence of pN1 disease after ePLND are eligible for the study. pN1 disease is defined as the presence of regional LN metastasis in the true pelvis. These regions include the common iliac nodes, presacral nodes, external and internal iliac nodes, and obturator nodes [27]. In all participating centers, performing an ePLND is the standard of care in high- intermediate and high-risk patients, independent of whether the primary treatment is RP or high-dose radiotherapy [7,28]. If pN1 disease is present, patients are eligible if one of the following criteria is fulfilled:

Two or more positive LNsPositive LNs/removed LNs >7%Presence of extracapsular metastatic extension at the level of any LN

ePLND is defined as the removal of LNs around the external and internal iliac vessels and in the obturator fossa. Removal of additional LNs in the presacral area or around the common iliac vessels is at the discretion of the treating physician (but strongly advised if present on preoperative imaging). The minimum harvest of removed LNs that is considered representative is set at 14. Textbox 1 summarizes the inclusion and exclusion criteria.

After amending, patients with pN1 disease in the salvage setting will be allowed in the PART trial and will be prospectively followed with the same treatment protocol and study design to obtain data about acute and late toxicity. These data will be analyzed separately and will not interfere with the initial set-up of statistics.

### Radiotherapy: Structure Delineation, Planning and Delivery

#### Structure Delineation

Details on delineation of the clinical target volume (CTV) of the pelvic nodal areas are provided elsewhere [29]. Briefly, the elective LN areas consisted of the obturator, internal and external iliac, presacral, and common iliac nodes [16]. Concerning the prostate bed (postoperative setting) and the prostate (primary setting), both T2-weighted magnetic resonance imaging (MRI) and computed tomography (CT) images are used to optimize delineation, as detailed elsewhere [30-32].

Delineation of the PALN starts caudally at the level where the abdominal aorta splits into both common iliac branches and stops cranially at the level of the renal artery and vein. The CTV of the PALN is created by adding a 7-mm 3-dimensional expansion to the abdominal aorta and inferior caval vein, excluding intestinal loops and vertebral bodies. Unless kidney function is impaired, CT imaging is done using intravenous contrast to optimize the visualization of the vessels and improve discrimination with the intestinal loops. The use of oral contrast to better visualize these intestinal loops is left at the discretion of the treating physician. Details concerning protocols on bladder filling and rectal preparation are provided elsewhere [33]. The planned target volume (PTV) of the LNs is created by expanding the CTV with an isotropic margin of 7 mm.

Concerning the organs at risk (OARs), the following structures are delineated: bladder, anal canal, rectum, sigmoid colon, small intestine, large bowel, femoral heads, spinal cord, cauda equine, bone marrow, and kidneys. Figure 2 depicts the delineation of the OARs.

#### Radiotherapy Planning

The applied planning technology is IMAT/VMAT/RapidArc (Varian Medical Systems, Palo Alto, CA, USA; Elekta, Stockholm, Sweden; Figure 3) [17]. The technology and feasibility to treat the PALN have been published [34].

Para-aortic radiotherapy (PART) trial: inclusion and exclusion criteria.
**Inclusion criteria**
Signed informed consent and willingness to comply with the treatment and follow-upDiagnosis of histopathologically confirmed prostate cancerNo former treatment for prostate cancer, except radical prostatectomy and extended pelvic lymph node dissection (ePLND)Presence of pathologically node-positive (pN1) disease after ePLND (criteria of pN1 disease defined in the protocol)Age >18 yearsKarnofsky Performance score >70Ability to understand the informed consent (Helsinki Declaration)
**Exclusion criteria**
Recurrent disease status defined as rising prostate-specific antigen after nadir postoperativelyPresence of cM1a, cM1b, or cM1c disease [27]; patients with cN1 disease at radiotherapy imaging for planning are excludedFormer radiotherapy, making whole pelvic radiotherapy (WPRT) or PART impossiblePrior malignancy, not disease-free >5 years, except basocellular skin epitheliomaSevere or active comorbidity likely to impact the feasibility of WPRT or PART (eg, ulcerative colitis)Disorder precluding the understanding of trial information

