### Primary Endpoint

The primary endpoint is 5-year clinical relapse-free survival (cRFS), defined as the absence of any cR that would be visible at top of the line imaging (see below). Any detected clinical recurrences (r) would be anatomically mapped and categorized as local (rL), pelvic nodal (rN1), retroperitoneal nodal (rM1a), bone (axial, perpendicular, or both, rM1b), or soft-tissue (rM1c). Combinations of different relapse sites are of course possible and will be reported accordingly. Apart from the anatomical site of relapse, the number of relapses, size per relapse, and the subsequent treatment will be recorded.

PSA measurements are performed during follow-up according to a fixed schedule (Table 1). If PSA is undetectable, patients are considered free of cR. In case of biochemical relapse, defined as PSA >0.2 µg/L in the postprostatectomy setting and PSA >nadir+2 µg/L in the primary setting [39,40]. In addition, positron emission tomography-CT (PET-CT) imaging using prostate-specific membrane antigen ligand or ^18^F/^11^C-choline- based PET-CT imaging is acquired. Additional imaging tools include multiparametric MRI and MRI of the axial and perpendicular bones. The decision to perform additional imaging will be taken after multidisciplinary consensus in all cases.

**Table 1 table1:** Standard Protocol Items: Recommendations for Interventional Trials 2013 diagram: Para-Aortic Radiotherapy (PART)-trial.

Timepoint		Study period					
		Enrollment: Screen visit & pre-PART (-t_1_)	Postallocation				
			During PART		Follow-up		
			Weekly	Last day	Month 1, 3, 6, 9, 12	Month 18, 24, 30, 36, 42, 48, 54, 60	Year 6 up to year 10, yearly

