### Sample Size and Statistics

We aim to improve 5-year cRFS by 15% (primary endpoint). This would result in a 5-year cRFS of 75% compared with the control group with WPRT only that reaches a 5-year cRFS of 60% [18,20]. For a log-rank test comparing two survival curves with a one-sided significance level of .1, assuming uniform accrual with an accrual time of 48 months and a follow-up time of 12 months, a sample size of 137 is required to obtain a power of at least 80%. Taking into account a dropout of 10%, we aim to include 151 patients. The control group consists of pN1 patients treated with adjuvant ADT and WPRT alone from whom the data have been published before [20]. The incidence of acute and late toxicity will be recorded. In addition, actuarial risk estimates for developing acute and late toxicity will be calculated using Kaplan-Meier analysis. Time to palliative ADT, time to CRPC, CSS, and in-field pelvic and para-aortic disease control will be calculated using Kaplan-Meier actuarial analysis. cRFS, time to CRPC, CSS, and in-field pelvic and para-aortic disease control times are defined from the date of LN dissection until an event or last follow-up. Statistical analysis will be performed using the latest version of SPSS (IBM Corp, Armonk, NY, USA).

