## Results

Ethical approval to conduct this study (version 2.0 from December 1, 2016) was granted by the Medical Ethics Committee University Hospitals/Catholic University Leuven (14/12/2016). Written informed consent of patients is mandatory before recruitment. Recruitment of patients started in 2017 and is expected to be completed by March 2020.

As a result of the PART trial, we will publish the 5-year cRFS, defined as the absence of any cR that would be visible at top of the line imaging, our primary endpoint. Furthermore, we will compare these results with the 5-year cRFS of a historical control group of patients who underwent WPRT; the results of this historical control group have already been published by Poelaert et al [20]. This control group includes patients with PCa who underwent PLND and pelvic radiotherapy between January 2000 and January 2016 at a tertiary center (GUH). Those patients were rigorously treated by several authors of this manuscript ([name], VF, [name], and NL). A total of 154 pN1 patients with PCa who received WPRT were included. As described in the “Sample size and Statistics” section, survival curves of both groups will be compared using log-rank test. Besides, acute toxicity and QoL results will be published after short-term follow-up, whereas treatment-related late toxicity and QoL results, time to palliative ADT, time to CRPC, CSS, and in-field pelvic and para-aortic disease control will be published after a longer follow-up period.

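### PART's imaging exclusions act after the cRFS clock starts and are not matched in the historical controls, so eligibility in the unadjusted log-rank test is not shown to be aligned

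*Protocol article*

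**What the plan says.** **PART entry.** The exclusion list (Textbox 1) bars cM1a, cM1b "or cM1c disease [27]; patients with cN1 disease at radiotherapy imaging for planning are" excluded. The section Inclusion and Exclusion Criteria also limits PART to pN1 men with at least one adverse nodal feature: two or more positive nodes, more than 7% of removed nodes positive, or extracapsular extension in any node.

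**Clock.** Sample Size and Statistics sets the origin for a list of endpoints that begins with cRFS: "disease control times are defined from the date of LN dissection until an event or last follow-up".

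**Event.** Primary Endpoint gives 5-year cRFS as "defined as the absence of any cR that would be visible at top of the line imaging". Detected recurrences are "categorized as local (rL), pelvic nodal (rN1), retroperitoneal nodal (rM1a"), bone or soft tissue.

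**Controls.** Sample Size and Statistics: "The control group consists of pN1 patients treated with adjuvant ADT and WPRT alone from whom the data have been published before". Results adds that they had PLND and pelvic radiotherapy at one tertiary centre between January 2000 and January 2016: "A total of 154 pN1 patients with PCa who received WPRT were included". No imaging exclusion and no nodal-risk restriction is stated for them.

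**Test.** A log-rank test at one-sided 0.10, for 75% against 60%. The article states no restriction, matching or adjustment.

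**The concern.** A man can enter PART only after dissection has shown pN1 disease, so the planning scan falls after time zero. PART is thus filtered on a disease finding made after its own clock has started. Men with nodes visible at planning, or with known metastases, plausibly relapse earlier than the rest. If such men stayed in the control series, the two curves differ for a reason unrelated to para-aortic irradiation. Restricting the controls on number of positive nodes would not remove the difference, because the filter works on imaging and not on pathology.

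At stake is the primary comparison, which the article offers as the basis for a later randomised phase III trial.

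**Working it through.** **The plan's own figure.** Take exponential survival, 48 months of uniform accrual and 12 months of follow-up.
- Hazard ratio = ln(0.75)/ln(0.60) = 0.563.
- Event probabilities: 0.259 (60% group) and 0.157 (75% group).
- Schoenfeld at one-sided 0.10 and 80% power: 55 events, 55/[(0.259 + 0.157)/2] = about 265 in total, or 132-133 per group. Freedman: 58 events, about 140 per group.
- With 137 per group, power is 0.81.

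The stated 137 is therefore reproduced as a per-group number. It takes for granted that the two groups differ only by treatment.

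**Size of the filter taken alone.** From the documents: control 5-year cRFS 60%, 154 controls, 151 PART patients, one-sided 0.10. Assumed, because the documents do not give them:
- share *q* of controls with cN1/cM1 at planning: 3-10%;
- 5-year cRFS *r* in those men: 20-40%;
- follow-up uniform on 36-84 months in both groups (48 months of accrual, centred on the 60-month median follow-up named in Time Schedule).

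With no treatment effect, the filtered group has cRFS = (0.60 − q·r)/(1 − q), and HR = ln(cRFS)/ln(0.60). With d1 and d0 expected events, the one-sided error is 1 − Φ(1.2816 + ln(HR)·√[1/(1/d1 + 1/d0)]).

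Worked case, q = 10%, r = 20%:
- cRFS = (0.60 − 0.02)/0.90 = 64.4%; HR = −0.439/−0.511 = 0.860; ln(HR) = −0.151.
- d1 = 53.2, d0 = 61.0; square-root term = 5.33.
- Error = 1 − Φ(1.2816 − 0.803) = 1 − Φ(0.478) = 0.32.

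| q | r | PART cRFS | Gain (points) | HR | Events | One-sided error |
|---|---|---|---|---|---|---|
| 0 | any | 60.0% | 0 | 1.00 | – | 10% |
| 3% | 40% | 60.6% | 0.6 | 0.98 | 120 | 12% |
| 3% | 20% | 61.2% | 1.2 | 0.96 | 119 | 14% |
| 5% | 40% | 61.1% | 1.1 | 0.97 | 119 | 14% |
| 5% | 20% | 62.1% | 2.1 | 0.93 | 118 | 18% |
| 10% | 40% | 62.2% | 2.2 | 0.93 | 117 | 19% |
| 10% | 20% | 64.4% | 4.4 | 0.86 | 114 | 32% |

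With 137 against 154 men and the shorter follow-up of the sample-size statement (12-60 months), the same formula gives about 12% to 26%.

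**What the table leaves out.** It isolates one filter. The nodal criteria for PART work the other way: the Introduction says that outcome worsens with the number of positive nodes and that extracapsular extension is an adverse factor. The documents give no control-group distribution of these features, so the two effects cannot be netted.

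**The case against.** The strongest objection is that the control series is a published cohort whose eligibility rules are in a paper not shown here. A one-line summary that mentions no imaging exclusion is not proof that none was applied. This stands, and makes the finding conditional. It does not settle the matter, because the article names the full published series as comparator and states no step that would align the two groups.

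Several stronger readings are tempting but not supported.
- *The controls entered merely for having received WPRT.* The text also requires pN1 disease, PLND and adjuvant ADT.
- *Nodes seen at planning are relapses under the plan's own definition.* Primary Endpoint ties imaging to biochemical relapse in follow-up and says "If PSA is undetectable, patients are considered free of cR". The exclusion uses the staging term cN1, not rN1. Such nodes may be residual disease, and the plan never counts them as events. The selection effect does not depend on the label.
- *The planning scan removes men already enrolled.* Study Design does say "After giving informed consent, they are included in the trial", but Table 1 puts eligibility screen, consent and baseline imaging in one pre-treatment column, so screen failure is the natural reading.
- *Better imaging caused stage migration in PART.* The planning imaging described is CT, usually with intravenous contrast, plus MRI for the prostate or its bed. Nothing shows that the controls' imaging was materially less sensitive.
- *The comparison as a whole is biased toward PART.* The nodal criteria push PART's cRFS down, so the net direction is open.

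It may also be said that control selection belongs in a full protocol or analysis plan. That is fair for detail, but the article does fix the comparator and the test, and as written they are not aligned.

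**Conclusion.** The concern holds in conditional form. PART applies cN1 and cM1a-c exclusions, the cN1 one on a scan after the cRFS origin, and the comparator as described carries no matching rule. If controls with such findings were kept, this filter alone adds about 0.6-4.4 points to PART's 5-year cRFS, against a target of 15, and moves the one-sided error from 10% to about 12-32%. These figures rest on an assumed share of 3-10%, an assumed cRFS of 20-40% in those men, exponential survival and the follow-up pattern above. The low end is small, and the effect is zero if the controls were screened alike. The documents do not support saying that PART's result will be inflated overall or that the 10% level is certainly lost. They support saying that the level is not protected, and that an inexpensive step would protect it against this source of bias.

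**What to change.** Before the log-rank comparison, apply PART's eligibility rules to the control records from existing staging, planning and pathology reports: the cN1 and cM1a-c exclusions together with the nodal criteria. Restrict the primary comparison to controls who meet them, and report how many were removed and under which rule. Show the comparison with all 154 controls as a sensitivity analysis. Both sets of rules should be applied together, since correcting only one could leave the other's bias unopposed.

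Planning-scan cN1 should not be counted as an event in PART only: that would impose early failures on one group with no counterpart in the other.

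The cost is chart review of up to 154 records, fewer controls with some loss of precision, and some reports that may be unavailable. Results says that several of the authors treated these patients, so access is plausible, but the article does not say that the reports are already in hand. Enrolment, treatment and the endpoint do not change.
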